**Methods:**

In a cross-over randomized controlled trial, 30 healthy young adults will experience HIE training in IVR (i.e. the virtual body will perform eight sets of 30 s of running followed by 30 s of slow walking, while the participant is completely still) according to two random-ordered conditions: during the experimental condition, the virtual body is displayed in first-person perspective (1PP), while in the control condition, the virtual body is displayed in third-person perspective (3PP). To confirm that individuals have the illusion of ownership and agency over the virtual body in 1PP (and not in 3PP), we will record the heart rate, in addition to subjective questionnaires. Before and after every IVR sessions (one week apart), we will measure cortical hemodynamic changes in the participants’ prefrontal cortex using the fNIRS device during the Stroop task’s execution.

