After that, the actual intervention consists of a vHIE performed by the virtual body exclusively: while seated, participants will see the virtual body (either in 1PP or 3PP) alternating 30 s of running and 30 s of slow walking, for a total of 8 min [17, 33]. After that, we will ask the participant to stay still and close his/her eyes, while we still record an extra 30 s of the HR (see the “Measurements” section) (see Fig. 2b). While the slow walking animation will be the same for all participants, in order to choose the speed of the running animation, after the familiarization phase, we will show four different options on the virtual body and individuals verbally report which one is subjectively perceived as considerably fast but feasible. This is necessary to maximize the possibility of having an actual physiological activation but, at the same time, to display an animation that is subjectively plausible so as to not break the illusion of ownership in 1PP.

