### Measurements

#### Heart rate

During the interventions, in order to check if participants actually perceive the virtual body as their own (in 1PP and not in 3PP), we will record the HR with a Polar H10 HR monitor, controlled by a specific application via Bluetooth. Participants have to wear an elastic strip around the chest on which the HR monitor is attached, positioning it close to the heart, in order to record the HR for each intervention conditions (1PP and 3PP) during the baseline (4 min), the intervention (4 min running, 4 min slow walking, for a total of 8 min) plus an extra 30 s (where the participant is still with closed eyes) to check for eventual delay in the recording and to wait for the synchronization of the HR.

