#### Online and offline questionnaires on SoBO and SoA

We will administer an online questionnaire for the subjective experience of SoBO and SoA. To control for eventual changes in subjective feelings during the intervention at different timepoints (in the middle of the baseline phase [i.e. after 2 min from the beginning if the IVR session], during the intervention at 1 min [i.e. while the avatar is running], at 2.5 min [i.e. while the avatar is slow walking ], at 5 min [i.e. while the avatar is running], and at 6.5 min [i.e. while the avatar is slow walking]), we will ask participants to rate their level of agreement (on a 1–7 Likert scale where 1 means “totally disagree” and 7 means “totally agree”) with respect to four statements: two of them (one is a “real statement” that checks for the actual presence of the illusion, while the other is a “control statement”) about SoBo and the other two about SoA (see Table 1) (see Fig. 2b).

**Table 1 Tab1:** Online questionnaire on SoBO and SoA

s1	SoBO	I feel as if I’m looking at my own body.
s2	SoBO control	I feel as if the virtual body belongs to another person.
s3	SoA	The virtual body moves just as I want, as if I am controlling it.
s4	SoA control	I feel as if the virtual body is controlling my will.

Questionnaire verbally administered during the vHIE (at 5 timepoints, at 2 min from baseline, and 1 min, 2.30, 5 and 6.30 min of vHIE) concerning the subjective participant’s feelings during the intervention. The statements s1 and s2 concern the SoBO, while the statements s3 and s4 concern the SoA. The statements s1 and s3 are “real statements” while statements s2 and s4 are “control statements.” Individuals will rate their level of agreement to the following statements on a 1–7 Likert scale (1 means “complete disagreement” and 7 means “complete agreement”).

Another questionnaire will be administered right after every IVR session (both after 1PP and 3PP intervention conditions) to check details for feelings of movement, motor control, and physical effort (see Table 2) (see Fig. 2 a). The statements are selected and adapted from previous studies [33, 41].

**Table 2 Tab2:** Offline questionnaire on SoBO and SoA

s5	Located	During the experiment, I felt as if my body was located where I saw the virtual body to be.
s6	Ownership	During the experiment, I felt that the virtual body was my own body.
s7	Standing	During the experiment, I felt that I was standing upright.

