s8	My movements	During the experiment, I felt that the leg movements of the virtual body were my movements.
s9	Agency	During the experiment, I felt that the leg movements of the virtual body were caused by my movements.
s10	Ownership control	During the experiment, I felt that the virtual body belonged to someone else.
s11	Effort	I felt I had to give extra physical effort when the virtual body was walking faster.
s12	Vection	I felt that I was moving through space rather than the world moving past me.
s13	Walking	I felt that I was walking.
s14	Dragged	I felt that I was being dragged.
s16	Sliding	I felt that I was sliding.

Questionnaire self-administered after the vHIE interventions concerning the subjective participant’s feelings during the previous intervention. The underlying explored domains are listed in the first column (not shown to the participant) while the corresponding statements are listed in the second column. Individuals will rate their level of agreement to the following statements on a 1–7 Likert scale (1 means “complete disagreement” and 7 means “complete agreement”).

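### The only effort item (s11) asks about the avatar walking faster, which this intervention never shows, so it is unclear which phase the answer describes

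*Protocol article*

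**What the plan says.** The abstract of the protocol article describes the virtual exercise as "eight sets of 30 s of running followed by 30 s of slow walking". The Interventions section repeats this as "alternating 30 s of running and 30 s of slow walking, for a total of 8 min", and the Heart rate section splits the time evenly between the two gaits. On speed, the Interventions section says "While the slow walking animation will be the same for all participants"; only the running animation is picked individually, from four options.

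The section on the online and offline questionnaires says that the offline form is given after each session "to check details for feelings of movement, motor control, and physical effort". In Table 2 the one statement labelled as effort is s11: "I felt I had to give extra physical effort when the virtual body was walking faster". Under Statistical analysis, the questionnaires and heart rate form the first phase, which checks whether the virtual intervention worked before the Stroop and fNIRS data are examined. The offline statements are to be compared between 1PP and 3PP. The Outcomes section classes the questionnaires as additional outcomes.

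**The concern.** The item names an event that the described session does not contain. Elsewhere the protocol treats walking and running as distinct: the heart-rate analysis codes running as the fast level and walking as the slow level, and the online rating times are labelled by one gait or the other. In the protocol's own terms, walking is the slow state.

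A participant asked about faster walking can answer in two ways. One is to rate the running phase as the nearest match. The other is to disagree because no such phase was seen. A low score then cannot separate no effort felt from no such event noticed. The heart-rate prediction is specific to running in 1PP, and the questionnaires are presented as its subjective counterpart. If heart rate rose during running and s11 stayed low, the team could not tell a real dissociation from a misread item.

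**Working it through.** **Inputs.** Eight sets of 30 s plus 30 s (abstract); total of 8 min (Interventions); 4 min per gait (Heart rate); one common slow-walking animation (Interventions); item texts (Tables 1 and 2).

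**1. Reproduce the stated duration.**
- Running: 8 × 30 s = 240 s = 4 min.
- Slow walking: 8 × 30 s = 240 s = 4 min.
- Total: 240 + 240 = 480 s = 8 min, which agrees with the plan.

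**2. Time left for any other gait.** 480 − 240 − 240 = 0 s. Walking speed is also fixed across participants, so nobody sees a faster walk.

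**3. Count the effort items.** Table 1 has 4 statements (s1 to s4), two on ownership and two on agency; none concerns effort. Table 2 has 11 (s5 to s14, plus s16); one, s11, concerns effort. That is 1 of 15 overall. The mood scale has no effort item among its eight terms.

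**4. What ambiguity does to the comparison.** The protocol gives no figure for how participants read the item, so this step is an assumption. Let p be the share who read it as running, and d their mean 1PP minus 3PP difference. Suppose literal readers disagree equally after both sessions and so contribute a difference of about zero. The expected observed difference is p × d + (1 − p) × 0 = p × d. It ranges from d (p = 1, no harm) to 0 (p = 0, no information). Mixed readings also add between-person variation, and a participant who reads the item differently in the two sessions adds noise to the paired difference. The documents do not place p within this range.

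**The case against.** The strongest defence is that the item has only one sensible referent. The caption to Fig. 2 describes the switch from slow walking to running as a change in the avatar's speed, the heart-rate analysis labels running as fast, and each participant has chosen a running animation seen as considerably fast. The session contains no other speed-up, so many participants may rate running anyway. This stands. A reader might infer that effort during running goes unmeasured; the documents do not support that, only that it is uncertain which phase a given answer describes.

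A reader might also infer that the questionnaires ignore the running phase, since no statement names running. That does not follow. Items s8 and s9 ask about the avatar's leg movements, which include running, and several other items refer to the experiment as a whole. Ownership and agency are rated online at 1 min and 5 min, both while the avatar runs. Heart rate is averaged separately for running.

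Nor does s13, "I felt that I was walking", contradict the design: walking is shown for 4 of the 8 min, and splitting that item would be a preference rather than a correction.

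Finally, no threshold or decision rule is attached to s11, so nothing in the plan would turn a low score into a declared failure of the illusion. The wording is the same after 1PP and 3PP, which limits systematic bias between conditions but does not remove the ambiguity. The text shown to the Japanese-speaking participants is not printed and may be clearer than the English.

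**Conclusion.** The point holds as a minor wording defect. The sole perceived-effort item refers to a phase that takes up 0 s of the 480 s session, so its answers may mix ratings of running with denials that faster walking happened. The likely result is a noisier, possibly diluted, 1PP versus 3PP effort comparison in the first-phase check. The amount cannot be stated, because it depends on how participants read the item.

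The conclusion assumes that the printed English reflects the administered item and that the session runs as described. It reaches one item of an additional outcome. The primary Stroop analysis, the fNIRS outcomes and the sample size are unaffected.

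**What to change.** Reword s11 so that it asks about extra physical effort while the virtual body was running. Use identical wording after 1PP and 3PP, and never change it between the two sessions of one participant, since that would break the paired comparison. No other item needs to change.

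The Trial status section says that recruitment began in February 2019. If data have already been collected, check whether the administered Japanese text separates faster walking from running, state which phase s11 was meant to cover, and interpret the item with caution. A mid-trial change should apply only to participants who have not yet had their first session; s11 would then have two versions across the sample, to be reported as such.

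The cost is one rewording and slightly less literal comparability with the source questionnaire, whose statements the protocol already describes as adapted.

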#### Stroop task

To measure the actual efficacy of the proposed intervention, we will record cortical hemodynamic changes in the participant’s PFC using the functional near-infrared spectroscopy (fNIRS) device before and after every IVR session (either 1PP and 3PP) during the execution of the color-word matching Stroop task (see Fig. 2 a).

We will adopt the Stroop task as previously used in several studies [17, 22, 46–48]. The Stroop task we plan to use consists of 30 trials, including 10 neutrals, 10 congruent, and 10 incongruent, presented in random order. For all trials, two words are displayed on the monitor one above the other: specifically for neutral trials, the upper row consists of XXXX printed in red, white, blue, pink, or yellow, and the lower row shows the words “RED,” “WHITE,” “BLUE,” “PINK,” or “YELLOW” printed in black. For congruent trials, the upper row contains the words “RED,” “WHITE,” “BLUE,” “PINK,” or “YELLOW” printed in the congruent color (e.g. RED was printed in red) and the lower row contains the same color words printed in black. For incongruent trials, the color word in the upper row is printed in an incongruent color (e.g. RED was printed in yellow) to produce cognitive interference between the color word and the color name (i.e. Stroop interference). All words were written in Japanese (hiragana). The lower row is presented 100 ms later than the upper row, in order to achieve sequential visual attention. Between each trial a fixation cross is shown, as an inter-stimulus interval, for 9–13 s to avoid timing prediction [17, 22, 49]. The stimulus remains on the screen for 2 s, independently from the participant’s answer. We will train participants to decide whether the color of the upper word (or letters) corresponds to the color name of the lower word by pressing button 1 on the keypad to give “yes” responses or button 2 to give “no” responses with their forefingers. Of the presented stimuli, 50% were correct (the correct answer is “yes”). We recorded response time (RT) and error rate (ER) as variable.

The Stroop task will be administered entirely via computer (to avoid biases due to presence of the researcher, especially concerning RT); for the present study, the Stroop task has been implemented using E-prime 2.0.

#### Functional near-infrared spectroscopy

We will use a wearable (without optical fibers) fNIRS optical topography system (WOT-HS, Hitachi Corporation & NeU Corporation, Japan). The NIRS headset (Fig. 3a) sends the signals to the Wearable Optical Topography High Sensitivity software Version 1.04 (Hitachi Solutions, Inc.) through a Control Box.

**Fig. 3 Fig3:**
[figure not shown]
The fNIRS system used in this study. **a** The headset of the fNIRS is shown on a mannequin. **b** Graphic representation of the detail and distribution of the capsules on the headset. Source: http://neu-brains.site/ [50]. Permission to reproduce the figure granted by NeU Corporation, Japan

This system is provided with 35 capsules, placed 3 cm away from each other, into which microprocessors, NIR emitting or high-sensitivity receiving sensors are packaged: the top and the bottom lines of the capsules alternate emitting and receiving sensors, while the central line comprises receivers only (Fig. 3 b); this new multi-distance measurement mode, including a total of 12 emitting and 23 receiving (11 of them are short-distance receivers) sensors, significantly reduces the biological noise on the hardware side, resulting in 34 channels over lateral and anterior PFC. The device will be positioned on the forehead by centering the specific mark on bottom line of probes at the Fpz (10% of the distance between Nasion and Inion), according to the international 10–20 system [51].

The device detects the concentration of oxygenated hemoglobin (O2Hb), deoxygenated hemoglobin (HHb), and total hemoglobin, calculated in units of millimolar-millimeter (mM·mm) [52], by applying two short-distance wavelengths of NIR light (850 nm, 730 nm) to monitor the above mentioned cortical hemodynamic changes in the PFC during the Stroop task [53].

#### Two-Dimensional Mood Scale

The Two-Dimensional Mood Scale (TDMS) is an effective measure to record changes in psychological mood states. The TDMS was developed as a psychometric scale using eight mood-expressing items (energetic, lively, lethargic, listless, relaxed, calm, irritated, and nervous) that, when combined, express mood states of pleasure and arousal [54]. We will ask participants to rate their present psychological state using a six-point Likert scale from 0 = “Not at all” to 5 = “Extremely” [17]. They will repeat the TDMS right before the pre-Stroop task (before the vHIE), as well as right after the post-Stroop task (after the vHIE) for each session (1PP and 3PP) (see Fig. 2a).

### Outcomes

#### Primary outcomes

Considering that the main goal of this study is to determine that vHIE intervention performed with the own virtual body (1PP) has a beneficial effect on cognitive executive functions, the primary outcome of this study is the Stroop task (i.e. the cognitive domain), specifically the two related measurements (RT primarily and ER secondarily). The Stroop task is considered the primary outcome here because it is widely known as a measure for executive brain functions [21, 55]. As a key effect of the Stroop task, we will consider the so-called “Stroop interference” as the (average of incongruent trials– average of neutral trials) contrast, which is assumed to represent Stroop interference, for both RT and ER in each condition (1PP and 3PP).

Specific timepoints (before and after the vHIE) will be considered, but the main comparison in order to find a significant effect of vHIE on cognitive functions will be 1PP versus 3PP.

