### Purpose

In this study, we combined the efficacy of the HIE on cognitive functions [17] with the possibility of manipulating SoBO and SoA offered by IVR [33, 41]. Our goal is to demonstrate whether a virtual HIE-based intervention performed exclusively by the considered-as-own virtual body, while the real individuals’ body is totally still (hereinafter vHIE), has acute cognitive and somatic beneficial effects on the real body, comparable to the ones that arise after actual physical training. We will compare the behavioral performance (speed and accuracy) with the Stroop task during the recording of the brain activity of the PFC with fNIRS (as in [15]), before and after the vHIE, in two interventions where we manipulate the visual perspective (1PP vs 3PP), known to induce or disrupt the SoBO and SoA over the avatar.

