### Interventions

Participants will visit the laboratory (located in the Smart-Aging Research Center) for two sessions, one week apart, corresponding to the two intervention conditions. In both sessions, the participants sit comfortably on a stool with their feet firmly resting on the ground and their arms relaxed by their sides. They have to wear the Oculus visor (oculus.com), equipped with two lenses that show the virtual world. They will be instructed to keep their bodies still but they can move and rotate their head, to explore the virtual body and the environment. The virtual environment, as well as the virtual bodies and the animations, is modelled in 3D Studio Max 2015 and implemented in Unity3D: it represents an open space with a green floor (simulating a meadow) and a natural-looking illuminated sky, with a visible horizon. Participants will see a gender-matched life-sized humanoid virtual body.

The intervention will be performed in two conditions. The experimental intervention displays the virtual body in 1PP, where the virtual body substitutes and is spatially coincident with the real one; in other words, to observe the virtual body, the participant has to look towards him/herself. The control intervention consists of displaying the same virtual body in 3PP, where the virtual body is collocated approximately 1.5 m to the left of the real participant’s body; in other words, to observe the virtual body, the participant has to rotate his head and look towards his left side.

In both conditions (1PP and 3PP), the intervention starts with a familiarization phase of 4 min (hereinafter baseline) where the gender-matched virtual body is displayed but there is no animation yet (i.e. the virtual body in both 1PP or 3PP is standing still). This phase is necessary to induce the illusory sensation of ownership over the virtual body (in 1PP) or not to induce it (in 3PP) (see the “Measurements” section for the online questionnaire on SoBO and SoA) for the baseline recording of the HR (see the “Measurements” section) and to check for eventual sickness problems due to the virtual display.

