#### Stroop task’s RT and ER

The second phase of the data analysis concerns the data collected before and after every IVR intervention, i.e. the results necessary to confirm our main hypothesis (the efficacy of IVR training on cognition).

As previously mentioned, in the Stroop task we will include two measurements, RT and ER: the (incongruent – neutral) contrast, which is assumed to represent Stroop interference, will be calculated. Both (RT and ER) will be analyzed by means of a repeated-measures ANOVA with TIME (before, after) and CONDITION (1PP, 3PP) as within-subject factors. As supplementary analysis, we will check for eventual differences between the two sessions considering only the Stroop task before the vHIE (predicting not differences). According to our hypothesis, we predict finding a shorter RT and lower ER after the vHIE in 1PP compared to 3PP.

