These results would contribute on different levels: from a theoretical perspective, this study would be another proof that the illusion of ownership over the virtual body is extremely effective and can be manipulated in order to arise effects on different levels (perhaps motor and cognitive). The simple fact that it is possible to show some effects consequent to the virtual illusion, comparable to the real ones, means the virtual movements are as effective as the actual ones. Our idea is that the SoBO (here the main variable manipulated through the perspective) can drive other aspects, such as motor function, and those, in turn, can drive others, such as cognitive functions. Theoretical models of motor control should clearly state the body and the sense of body ownership as a variable that can significantly affect the resulted action [68, 69].

From a clinical perspective, these results will have interesting applications: as previously mentioned, the intervention presented here can be very useful for sedentary people or those suffering from cardiopathy to start physical activity in a totally safe and entertaining way, or combining cardio or power exercise, and the IVR training, maximizing the efficacy of both on somatic and cognitive terms. In more extreme situations, patients with motor disorders can perform the virtual training but with the same beneficial effects as physical training [70].

However, this study has some limitations. All participants have to repeat the Stroop task four times (before and after the two IVR sessions). This could have a learning effect, or an effect due to the repetition itself, as a negative consequence. To avoid this, we will randomize the order in which the intervention conditions will be administered, but it is still possible to have a repetition effect. Another potential limitation concerns the control conditions of the intervention: several previous studies using IVR exploit the 3PP as a control condition. In some cases, it seems to have a sort of effect, although the reported effect is smaller than the one of the experimental condition. Finally, a difference between the previous study with a similar design and the current one concerns the type of intervention: in Kujach et al. [17], the training consists of a cycling exercise, while in our study we decided on a running exercise in order to be as consistent as possible with other previous studies with similar IVR setup [33].

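### The 1PP–3PP contrast estimates the effect of visual perspective during one and the same virtual exercise, not the efficacy of virtual exercise that the plan says it tests

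*Protocol article*

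**What the plan says.** **What differs between the conditions.** The Purpose section describes a before-and-after comparison "in two interventions where we manipulate the visual perspective (1PP vs 3PP". Under Interventions, "The control intervention consists of displaying the same virtual body in 3PP", placed beside the participant instead of coinciding with the participant's own body. The exercise content is common to both sessions: "participants will see the virtual body (either in 1PP or 3PP) alternating 30 s of running and 30 s of slow walking", for 8 minutes in total.

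**What is tested.** Stroop interference (incongruent minus neutral) is analysed by a "repeated-measures ANOVA with TIME (before, after) and CONDITION (1PP, 3PP) as within-subject factors" (Stroop task's RT and ER).

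**What the test is said to show.** Under Primary outcomes the goal is to determine that "vHIE intervention performed with the own virtual body (1PP) has a beneficial effect on cognitive executive functions", and "the main comparison in order to find a significant effect of vHIE on cognitive functions will be 1PP versus 3PP". The Stroop analysis section says these results are needed to confirm the main hypothesis, glossed as "the efficacy of IVR training on cognition". The Discussion goes further. If the hypothesis is confirmed, it would conclude that virtual training produces the same consequences as real training and that virtual movements are as effective as actual ones.

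**What is conceded.** The limitations paragraph of the Discussion says of 3PP as a control: "In some cases, it seems to have a sort of effect, although the reported effect is smaller than the one of the experimental condition". It also allows for a learning or repetition effect over the four Stroop administrations. None of the conclusions is narrowed as a result.

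**The concern.** To claim an effect of virtual exercise, one needs a comparison with a condition that lacks it. Here the exercise programme is constant across conditions and only the viewpoint varies. The planned contrast answers whether perspective matters while the exercise is watched. The plan labels that answer as efficacy of vHIE, or of virtual-reality training, on cognition.

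What is at stake is the headline inference. A significant 1PP advantage would be reported as evidence that virtual training improves executive function, and clinical uses are already proposed on that basis. The design supports a narrower statement: seeing the exercising body as one's own changes Stroop performance relative to seeing it as someone else's.

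**Working it through.** The plan gives no figure for this point. Its sample size of 28 rests on an unquantified moderate effect and does not bear on what the contrast identifies. The check is therefore algebra, followed by an illustration on stated assumptions.

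**1. What the contrast estimates.** Take as reference an equal interval between two Stroop tests with no virtual exercise. Let P be the practice or repetition change common to both sessions, and let E1 and E3 be the effects of the 1PP and 3PP sessions against that reference.

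- Change in 1PP = P + E1
- Change in 3PP = P + E3
- TIME × CONDITION contrast = (P + E1) − (P + E3) = E1 − E3

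P cancels, which is the strength of the paired design. Neither E1 nor E3 is estimated by itself. The contrast equals E1 only if E3 = 0.

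**2. Why E3 = 0 does not settle it.** Split each effect into viewing the body without exercise (V) and the added contribution of the exercise content (X): E1 = V1 + X1 and E3 = V3 + X3. Then

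E1 − E3 = (V1 − V3) + (X1 − X3).

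With an inert 3PP condition this becomes V1 + X1. If exercise content contributes nothing (X1 = 0) and first-person viewing alone gives a benefit B, the contrast is B. Separating V1 from X1 needs a Stroop test after a 1PP avatar that does not exercise. The static avatar appears only in the 4-minute familiarization phase, and no Stroop test follows that phase before the exercise begins.

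**3. Whether before–after change can substitute.** Within 1PP the change is P + E1. The Discussion allows P to be non-zero, so this does not isolate E1 either.

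**4. Size, for illustration only.** If 3PP delivers a fraction f of the 1PP benefit, the contrast is E1 − f·E1 = (1 − f)E1:

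| f (assumed) | Share of E1 shown |
|---|---|
| 0.3 | 70% |
| 0.5 | 50% |
| 0.7 | 30% |

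A simulation used n = 30, 40,000 runs and two-sided α 0.05. The SD of the 1PP-minus-3PP change was set to 1, the two change scores were independent, and a common practice gain of 0.5 was assumed:

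| Assumed benefit against no exercise (SD) | Chance of a significant 1PP advantage |
|---|---|
| 1PP 0.5, 3PP 0 | 75% |
| 1PP 0.8, 3PP 0.5 | 36% |
| 1PP 0.5, 3PP 0.5 | 2.6% |
| Neither | 2.3% |

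In the last row, where virtual exercise does nothing, a before–after test within 1PP alone is still significant in 96% of runs, purely from the assumed practice gain. The effects, SD and practice shift are assumptions, not values from the documents.

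**The case against.** **The question is already about the owned body.** The Abstract, the Purpose section, the stated goal under Primary outcomes and the Discussion all frame the study partly around ownership and agency, and the prediction in the Stroop section is worded as 1PP compared with 3PP. For that question, an unowned body doing identical exercise is a coherent matched control. This stands: 3PP is not a wrong comparator, and the analysis need not change. But the protocol also uses vHIE for both conditions and states its conclusion as efficacy of vHIE and of virtual-reality training, which is a different claim.

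**The manipulation checks cover the rival explanations.** Heart rate is compared between running and walking, each against a static baseline, and the offline questionnaire asks about effort, vection and walking. This stands for heart rate and for subjective experience. These data test embodiment. They do not show that 3PP is cognitively inert, and the Stroop outcome has no corresponding exercise contrast.

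**The limitation is disclosed.** It is in part. The Discussion mentions a possible 3PP effect but not that exercise content is never varied, and its conclusions stay as broad as before.

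**Stronger readings that the documents do not support.**
- A reader might infer that the plan will take a null result as proof that virtual exercise does not work. No section says how a null would be read; the Discussion covers only confirmation.
- A reader might infer that a null is as likely as a difference. The Discussion describes the 3PP effect as the smaller one, which points to an attenuated difference in the same direction. The equal-benefit row above is a limiting case.
- A reader might infer that within-condition change will be offered as evidence of efficacy. The plan subordinates the time points to 1PP versus 3PP.
- A 1PP advantage could also arise because 3PP worsens performance. Nothing in the documents suggests this, and it is given no weight here.

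**Conclusion.** The point holds as a mismatch between contrast and conclusion. The planned comparison validly estimates the effect of visual perspective, or embodiment, on the change in Stroop interference while the same virtual exercise is watched. It does not estimate the effect of vHIE or the efficacy of virtual-reality training on cognition. Reading it that way requires an inert 3PP condition, which the protocol itself doubts. Attributing the result to exercise content would also require a non-exercising 1PP comparison, which the design lacks.

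The identification argument needs no numerical assumption beyond a practice effect common to both sessions. The size of any understatement cannot be derived from the documents; the 30% to 70% range follows only from the assumed f and from a 3PP effect in the same direction as the 1PP effect. The trial remains informative on the narrower question.

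**What to change.** Change the wording in three places.

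1. **Primary outcomes and Stroop task's RT and ER.** State the primary question as the effect of perspective (1PP versus 3PP) on the before-to-after change in Stroop interference, following the same virtual exercise. Replace the references to an effect of vHIE and to the efficacy of virtual-reality training.
2. **Interpretation.** State that a 1PP advantage will be attributed to perspective or embodiment and not to exercise content. Add that, if 3PP viewing itself gives some benefit, the contrast understates any vHIE effect.
3. **Discussion.** Bring the conclusions into line. The statements that virtual training has the same consequences as real training, and that virtual movements are as effective as actual ones, go furthest beyond the design, which also has no real-exercise condition. The clinical applications should be presented as needing further study.

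No new condition, participant or analysis is needed, so the change can be made whatever the stage of recruitment. The cost is a narrower headline claim. Keeping the broader claim would require a Stroop-tested condition without virtual exercise, which is a different and larger study.
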